### Patient and Public Involvement Engagement

This study was discussed and shaped with patient and public involvement engagement (PPIE) through dedicated workshops before the funding submission. The PPIE group agreed with the importance of developing a more robust research base for treatments that can improve the primary care management of MSK pain. Their discussions informed the design and piloting of the text message system and 1-page postal questionnaire used to capture the primary outcome of pain intensity. They also reviewed and improved the patient-facing documentation for the study. Members of the group have expressed an interest in being involved in the analysis of the qualitative data, and it is intended to include them in that process.

Further PPIE meetings were held following the feasibility and pilot trial to identify improvements for the main trial. Their recommendations included the following:

Updating the invitation pack to provide greater clarity to patients about what is involved in taking part in the trial.Simplifying the consent form in the initial patient questionnaire.Removing the prize draw system used for participants in the feasibility and pilot trial. This was considered to potentially be confusing for patients and did not appear to lead to a higher response rate to the questionnaires than those in similar research studies.

### Outcomes

#### Primary Outcome

The primary outcome for the trial is the patient-reported clinical outcome of pain intensity, measured monthly over 6 months. Pain intensity is a recommended outcome for trials of MSK pain [37] and had strong face validity among members of the PPIE group. In addition, analysis of our previous MSK cohort data confirmed that this outcome is sensitive to changes in this population.

#### Secondary Outcomes

Secondary clinical outcomes captured at the initial and 6-month questionnaire include body site–specific physical functional measures, using the Roland-Morris Disability Questionnaire for patients with back pain [38], the Neck Disability Index [39,40] for patients with neck pain, the Shoulder Pain and Disability Index [41] for patients with shoulder pain, the Knee Injury and Osteoarthritis Outcome Score-Physical Function Short form [42] for patients with knee pain, and the Short Form 12v2 Physical Component Scale [43] for patients with multisite pain. Other clinical outcomes will include patients’ risk of persistent disabling pain using the Keele Start MSK Tool, and the impact and severity of their MSK pain using the MSK-HQ [34], which includes measures of pain interference with sleep, physical activity level, hobbies/leisure activities, work and daily routine, and quality of life with items for patients’ confidence in managing their pain (pain self-efficacy) and emotional health and understanding of how to deal with their condition. We will also collect fear-avoidance beliefs using the 11-item version of the Tampa Scale of Kinesiophobia [44], and the patient-perceived level of reassurance from their clinician will be captured using the Holt and Pincus [45] reassurance scale, which has 4 subscales: information gathering, relationship building, generic reassurance, and cognitive reassurance. Other outcomes will include health-related quality of life using the EQ-5D-5L to calculate QALYs in the health economic evaluation [46] and single-item questions to capture patient satisfaction with care received, receipt of written education material from their clinician, and overall rating of change in their MSK pain since their primary care consultation [47]. As completion of the initial questionnaire can occur up to 4 weeks following the index MSK GP consultation, this means the first measurement of secondary outcomes is after the commencement of treatment. We chose the timing of the final outcome to be at 6 months as our pilot trial [21] demonstrated a plateau in mean outcomes before this time point. A summary of the patient data collection variables is listed in Table 1.

### Baseline Population Descriptors

To help describe the population recruited, additional baseline descriptors will capture health literacy using the Single Item Literacy Screener [48], episode duration of MSK pain by asking time since last whole month free from this pain, age, sex, employment, and their most recent paid job title (to calculate their socioeconomic status).

### Health Care Resource Use

Questions on additional health care resource use and patient-borne costs including MSK pain–related hospital inpatient stays, outpatient attendance (eg, physiotherapy), other NHS and private practice health care appointments, and over-the-counter medicines and treatment will be included in the 6-month questionnaire. Work performance will be assessed through a single-item work presenteeism question, and time (days) off work will be aligned to occupational information to ascertain the cost of absenteeism.

### Process Evaluation

A process evaluation is planned to explore a range of potential factors that might influence differences between trial arms as well as to better understand how stratified care is used and perceived by patients and clinicians. Following recent Medical Research Council guidance on process evaluations for complex interventions [49], we have designed a mixed methods approach [50]. This will use quantitative analyses focusing on a priori hypothesized intervention targets and qualitative approaches using focus groups and interviews.

A key aim of the process evaluation is to better understand the role of potential intervention targets (mediators) on differences in outcomes between the trial arms [51]. The evidence from our previous stratified care trial (for back pain, the Start Back trial) suggested that the identification and targeting of psychological distress among patients at high risk led to improved outcomes [52]. In addition, a systematic review has recently summarized available evidence and identified pain self-efficacy as another potential mediator [53]. Evidence from the Keele Implementation to Improve Patient Care through Targeted treatment Back study [20], which sought to implement our stratified care approach for patients with low back pain consulting in general practice, suggested that important clinical behavior changes included more systematic identification of patients who are *at risk* of persistent disabling pain who need additional support (leading to more referrals to physiotherapy). After careful consideration by the trial team, a number of potential treatment mediators have been identified a priori, including 3 potential factors at the patient level: (1) reduction in levels of psychological distress measured each month with a single item, (2) increases in pain self-efficacy measured each month with a single item, and (3) the extent of patient-perceived reassurance during the index primary care consultation measured via the initial questionnaire. Changes in these potential patient-level treatment mediators will be examined within a mediation analysis using causal modeling techniques (eg, structural equation modeling) to confirm if they are in the causal pathway explaining any observed between-arm differences in outcome with results also examined at each subgrouping level (low, medium, and high).

In addition, we have identified a number of a priori potential mediators at the level of clinical behavior, measured using the medical record data, including the proportion of patients who receive prescription medications for MSK pain, referrals to other services (eg, physiotherapy and secondary care specialists), referrals for investigations (eg, radiographs, MRI/Computerized Tomography (CT) scans, blood tests), sick certifications (fit notes), and further MSK-related consultations. We will test if there are significant differences in these behaviors between intervention and control practices and whether any of these differences are associated with the results in terms of patients’ pain intensity.

### Sample Size

In an average-sized UK general practice (6000 registered adults), we expect that about 800 potentially eligible patients will consult with the MSK pain sites of interest per year or 400 over 6 months. The feasibility and pilot trial showed that, on average, the template was activated 375 times over 6 months in each practice, and clinicians fully completed it in 41.1% (154/375) of cases (6 times per week), leading to a letter inviting the patient to participate in the data collection. From this, we expect that 40% of patients invited will return their initial questionnaire in the main trial, be eligible, and consent to further data collection (or 62 over 6 months in 1 practice). However, to be more cautious, given the general uncertainty in data and in generalizability of pilot estimates, we have conservatively estimated the average number of participants recruited per practice within 6 months in the main trial to be around 33% of those invited (or n=50 in 6 months or n=9 per month per practice).

The trial is powered at 90% to test the hypothesis of the overall superiority of stratified primary care versus usual care based on an alpha of 5% (two-tailed) to detect a small *effect size* (standardized mean difference) of 0.2 [54] in the primary outcome (pain intensity). An effect size of 0.2 was considered to be appropriate based on information from the feasibility and pilot trial, in which the proportion of responders in the 3 risk subgroups was 32% at low risk, 55% medium risk, and 13% high risk. Our previous trial of stratified care for patients with low back pain (the Start Back trial) found an effect size of 0.3 and 0.4 in the primary outcome (back pain–related physical function) in patients at medium and high risk, respectively. Therefore, we have assumed these standardized differences in this new trial [19]. In addition, the minimal clinically important difference for the numerical rating scale (NRS) pain intensity scores in MSK pain has been reported to be 1 point [55], which equates to an effect size of about 0.4, relative to an expected SD of about 2.5 [54]. We expect that there would be little or no difference between stratified care and usual care for patients in the low-risk subgroup. Hence, by multiplying these effects by the expected proportion within each subgroup, the overall effect size of interest is 0.2 (equating to an absolute mean difference of approximately 0.5 in pain intensity on a 0-10 scale).

The sample size calculation takes into account the clustering of individual participants by practice and likely participant dropout over a 6-month follow-up (inflationary effects on sample size requirement) as well as repeated measurements and adjustment for corresponding baseline pain intensity score (deflationary effects). We have allowed for an Intraclass correlation coefficient of 0.01 based on previous patient-level data from primary care trials [56] as well as expected variation in recruitment per practice using a guideline coefficient of variation of 0.65 [57], and together with an expected loss to follow-up across all time points of approximately 25%, these factors combine to give a sample size inflation factor of ×2.3 (based on an average cluster size of approximately 50 participants per practice in 6 months). The correlation of data within 6 repeated measurements and correlation of follow-up scores with baseline score are typically 0.7 and 0.5, respectively [58], which combine to give a sample size deflation factor of ×0.5. The product of inflation and deflation effects results in a magnification of 1.15 compared with a conventional, individual patient, single follow-up comparison, whereby the sample size requirement would be 525 per trial arm (or 1050 in total). The adjusted sample size target is, therefore, 600 patients per arm (1200 in total) from 24 general practices (12 per arm).

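### The 90% power holds only if the ICC of 0.01 belongs to the baseline-adjusted six-month mean, which the protocol does not say; on a single-score ICC, power on 22 df is roughly 81–88%.

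*Protocol article*

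**What the plan says.** All the inputs are in the Sample Size section of the protocol article. The power claim carries no qualification: "The trial is powered at 90% to test the hypothesis of the overall superiority of stratified primary care versus usual care". The test is two-sided at the 5% level, and the standardised difference sought is a small one. The target is given as "the overall effect size of interest is 0.2 (equating to an absolute mean difference of approximately 0.5 in pain intensity on a 0-10 scale".

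For clustering: "We have allowed for an Intraclass correlation coefficient of 0.01 based on previous patient-level data from primary care trials". Unequal practice sizes enter through "expected variation in recruitment per practice using a guideline coefficient of variation of 0.65", and dropout is taken as about 25%. Together these give a "sample size inflation factor of ×2.3 (based on an average cluster size of approximately 50 participants per practice in 6 months".

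Six repeated scores with mutual correlation 0.7 and a baseline correlation of 0.5 then give a deflation factor of 0.5. The two factors are multiplied: "The product of inflation and deflation effects results in a magnification of 1.15 compared with a conventional, individual patient, single follow-up comparison". Applied to 525 per arm, this leads to 600 per arm from 12 practices per arm.

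The section Main Analysis of Primary Outcomes specifies a three-level mixed model with practice as the top level. It is adjusted for age, sex, point-of-consultation pain and practice size, and focuses on the average effect over months 1 to 6.

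**The concern.** The deflation factor describes what averaging and baseline adjustment do to a patient's score. A stable difference between practices is shared by all six scores of every patient in the practice, so averaging those scores does not reduce it. Multiplying the whole design effect by 0.5 treats the practice component as halved too. That is legitimate only if the ICC was measured on the averaged, adjusted score in the first place.

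The protocol attaches no outcome form to the 0.01. It lists the ICC with the inflation effects, introduces repeated measures and baseline adjustment separately as deflation effects, and makes the comparison with a single follow-up. A reader would more naturally take 0.01 as a single-score ICC.

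Separately, the 525 per arm comes from normal quantiles, while the arm effect is a comparison of 24 randomised practices.

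At stake is how a null result is read. Readers will judge what the trial can exclude partly from its stated power.

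**Working it through.** **Inputs (Sample Size section).** Two-sided alpha 0.05; power 90%; effect 0.2; ICC 0.01; coefficient of variation (CV) of cluster size 0.65; mean recruited cluster size 50; loss 25%; six scores with correlation 0.7; baseline correlation 0.5; 600 per arm in 12 practices per arm.

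**1. Reproduce the plan.**
- Individual, single follow-up: 2 × (1.96 + 1.2816)² / 0.2² = 525.4 per arm (stated 525).
- Design effect: 1 + [(1 + 0.65²) × 50 − 1] × 0.01 = 1.701. Divided by 0.75 this is 2.27 (stated 2.3).
- Deflation: (1 + 5 × 0.7)/6 − 0.5² = 0.75 − 0.25 = 0.50 (stated 0.5).
- 525.4 × 2.268 × 0.5 = 596 per arm; with the rounded factors, 525 × 1.15 = 604. Both agree with 600.

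**2. What the product assumes.** Scale the single-score variance to 1. The analysed score then has variance 0.5. Multiplying the factors keeps the ICC at 0.01 on that scale, so the practice variance becomes 0.01 × 0.5 = 0.005. If 0.01 is a single-score ICC, the practice variance is 0.01. If none of it is removed, the ICC of the analysed score is 0.01/0.5 = 0.02. If baseline adjustment removes a quarter (an assumption, for illustration), it is 0.0075/0.5 = 0.015.

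**3. Cluster size.** The plan's design effect uses 50 recruited per practice. After 25% loss, 50 × 0.75 = 37.5 are analysed, which is 450 per arm. Using 37.5 with 450 is consistent, and it favours the plan.

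**4. Power at 1200 enrolled.** V = 2 × 0.5 × DE / 450, with DE = 1 + [(1 + 0.65²) × m − 1] × ICC. Power is taken from the normal distribution, or from the noncentral t on 24 − 2 = 22 df, with noncentrality 0.2/√V.

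| ICC of analysed score | m | DE | V | Normal | t, 22 df |
|---|---|---|---|---|---|
| 0.01 (plan's inputs) | 50 | 1.701 | 0.003781 | 90.2% | 87.4% |
| 0.01 | 37.5 | 1.523 | 0.003385 | 93% | 91% |
| 0.015 | 37.5 | 1.785 | 0.003967 | 89% | 86% |
| 0.02 | 37.5 | 2.047 | 0.004549 | 84% | 81% |

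Deflating only the within-practice part explicitly (within 0.99 × 0.5 = 0.495, between 0.01) gives V = 2 × (0.495 + 37.5 × 1.4225 × 0.01)/450 = 0.004571, and again 81% on 22 df.

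**5. Mixed-model weighting.** The design effect with the CV term does not credit a mixed model's more efficient weighting of unequal practices. With gamma-distributed practice sizes (an assumption; CV 0.65, mean 37.5) and optimal weights, power on 22 df is 84% at ICC 0.02, 88% at 0.015 and 92% at 0.01.

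**The case against.** The strongest reply is that the protocol never calls 0.01 a single-score ICC. It cites earlier primary care trial data, which cannot be seen here. If that figure was estimated on a baseline-adjusted average, the product is right and power is 91% on 22 df with analysed cluster sizes. This stands: the scale of the ICC is not proven either way.

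The value 0.02 is also an upper bound. It needs averaging and adjustment to leave the practice variance untouched, whereas the primary model adjusts for baseline pain and practice size, and averaging can smooth practice differences that vary from month to month. This stands too, and is why a range is given.

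The subgroup effects in the Sample Size section give 0.55 × 0.3 + 0.13 × 0.4 = 0.217 before rounding. At 0.217, ICC 0.02 and 37.5 per practice, power on 22 df is 87%. However, the stated target is 0.2, and 87% is still below 90%.

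Three stronger readings are tempting and not supported:
- **Power is demonstrably nearer 80%.** That takes the unproven ICC scale as fact and the upper bound as the central case.
- **Power may be as low as 74%.** That figure (ICC 0.02, m = 50, 22 df) pairs 450 analysed per arm with a cluster size of 50, which would be 12 × 50 = 600 per arm.
- **The planned confidence intervals are too narrow.** The protocol does not specify normal-based or maximum-likelihood inference, and the degrees-of-freedom method is a detail the separate analysis plan may fix.

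**Conclusion.** There is no arithmetic slip. The flaw is an unstated condition: the stated 90% needs the ICC of 0.01 to describe the baseline-adjusted six-month mean, and the text neither says this nor suggests it.

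At effect 0.2, with 25% loss, CV 0.65, 37.5 analysed per practice and 22 df:
- single-score ICC, no practice variance removed: about 81%, or 84% with optimal weighting;
- single-score ICC, a quarter of practice variance removed: about 86–88%;
- ICC already on the analysed scale: about 91%, or 87% at the plan's own cluster size of 50.

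The degrees-of-freedom point does not depend on the ICC reading, but it is small: about 3 percentage points at the plan's own inputs (90.2% to 87.4%). The unqualified 90% is therefore not secured, though it is not shown to be wrong under every reading. The design remains reasonable.

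**What to change.** Keep 1200 patients and 24 practices; the Results section reports recruitment complete at 1203. In the Sample Size section, or in the report of the trial:

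1. State which form of the outcome the ICC of 0.01 refers to: a single score, the six-month average, or the baseline-adjusted average.
2. If it is a single-score ICC, apply the 0.5 only to the within-practice variance and restate power as roughly 81–88%, computed on 22 df. If it is the ICC of the baseline-adjusted mean, say so, cite it as such, and give power on 22 df (87% at cluster size 50, 91% at 37.5).
3. As a low-cost recommendation rather than a proven omission, confirm that the primary model is fitted by REML with Kenward-Roger or Satterthwaite degrees of freedom for the arm effect.

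The cost is a few sentences, possibly a less favourable stated power, and at most one model option. Nothing in the design or data collection changes.

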### Statistical Reporting

Data will be reported according to the Consolidated Standards Of Reporting Trials (CONSORT) 2010 statement [59,60], including extensions to cluster randomized trials [61] and pragmatic trials [62].

Final analysis will be carried out after all the data are collected, entered, and cleaned according to Keele CTU SOPs. A flow diagram will show the flow of participants through the trial, including reasons for not taking part and loss to follow-up (split by trial arm). For trial participants, summaries of continuous variables will comprise the number of observations used, mean, median, SD, and interquartile range as appropriate for the distributional form of the data (in total and split by treatment arm). Summaries of categorical variables will comprise the number of observations used and the number and percentage of observations in each category.

Inferential analyses will include reporting of the main (point) estimate for the mean between-arm difference (numerical outcomes) or odds ratio (categorical outcomes) along with 95% CI and *P* values (two-tailed). Odds ratios will also be converted to absolute risk differences (using the usual care prevalence as the base reference in any conversion). Hypothesis tests will use a two-sided 5% significance level. The main analyses will be performed independently by the trial statisticians using the protocol, and the statistical analysis plan agreed with the TSC. For any results discordance(s), if consensus agreement cannot be reached, then a third (independent) statistician will be asked to review and resolve any differences.

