#### Main Analysis of Primary Outcomes

To avoid any potential bias in the analysis, intention to treat (ITT) will be the primary analysis population (including primary and secondary outcomes) unless otherwise stated in the detailed statistical analysis plan (available from the authors). This is defined as general practice clusters (and affiliated participants) being analyzed as they are randomized regardless of the intervention. Data for individuals who withdraw consent to participate in data collection will be included up to the point of withdrawal. Primary analysis will compare mean differences in pain intensity scores between trial arms over a 6-month follow-up using a hierarchical linear mixed regression model evaluating repeated measures data at 1-, 2-, 3-, 4-, 5-, and 6-month follow-up (level 1) within individuals (level 2) and taking into account clustering of individuals within general practices—the unit of randomization (level 3). The analyses will be adjusted for age, sex, and baseline pain intensity score (recorded from the IT template at the point of consultation) at the individual-patient level and general practice size. This analysis fulfills the ITT principle with analysis as randomized and missing data being accounted for under the missing at random assumption. Although the primary analysis will focus on the *average* intervention effect across 1 to 6 months of follow-up, we will also use treatment by time interaction terms to evaluate between-arm differences in mean responses across each of the individual time points of 1, 2, 3, 4, 5, and 6 months. Model fit will be assessed across different covariance structures (unstructured, independence, exchangeable, autoregressive) to ascertain the best-fit model that will be implemented (ie, the model that gives the lowest Bayesian Information Criterion, Akaike Information Criterion, and highest log-likelihood statistics). The monthly pain intensity scores will be used; however, if, for any individual, the last monthly SMS/brief questionnaire response is missing but they have completed the corresponding pain intensity question in their returned 6-month questionnaire (if completed within 20 days of the date of issue of their monthly SMS/brief questionnaire), then the available pain intensity score response will be used (as the 6-month score) for purposes of the primary outcome evaluation.

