#### Analysis of Secondary Outcomes

Analysis of secondary outcomes will be carried out using the ITT approach and using a linear mixed model for numerical outcomes and generalized mixed logistic models for categorical outcomes (adjusted for age, sex, baseline pain, and corresponding baseline score [where applicable] at the individual-patient level and general practice size). For monthly follow-up measures of distress and confidence in managing pain, the analysis will follow that of the primary analysis with initial focus on *average* scores over the 6 months of follow-up and then the time-specific between-arm estimates. The focus of the other secondary measures is on 6-month follow-up data only, with the exception of perceived reassurance, which is captured in the baseline questionnaire.

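### Applying adjusted mixed-model odds ratios to the usual-care prevalence can overstate the absolute risk difference for categorical secondary outcomes

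*Protocol article*

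**What the plan says.** Two parts of the protocol article together fix the method.

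- Statistical Reporting: inferential results are given as "mean between-arm difference (numerical outcomes) or odds ratio (categorical outcomes) along with 95% CI". Then: "Odds ratios will also be converted to absolute risk differences (using the usual care prevalence as the base reference in any conversion". The words about any conversion make this a general rule. No formula is given, and the section does not say whether the prevalence is observed or model-predicted.
- Analysis of Secondary Outcomes: the models are "generalized mixed logistic models for categorical outcomes (adjusted for age, sex, baseline pain, and corresponding baseline score [where applicable", and general practice size is a further covariate.

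The primary outcome lies outside the rule: "Primary analysis will compare mean differences in pain intensity scores between trial arms over a 6-month follow-up".

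**The concern.** A logistic mixed model adjusted for covariates estimates the odds ratio for patients with the same covariate values in the same practice. The usual-care prevalence averages over all those patients. Where covariates predict the outcome, the conditional odds ratio lies further from 1 than the odds ratio comparing the two arms as whole groups, even when the arms are perfectly balanced. Applying it to the average usual-care risk therefore does not return the difference between the arms' average risks. In expectation, the result is too far from zero, whichever arm does better.

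At stake is the absolute difference shown beside each categorical secondary result, which is its most readable form.

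**Working it through.** **Is there a figure to reproduce?** No. The protocol gives no prevalence, odds ratio or risk difference for any categorical outcome, so the size can only be illustrated.

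**Inputs from the protocol (Sample Size)**
- "Intraclass correlation coefficient of 0.01 based on previous patient-level data from primary care trials".
- "correlation of follow-up scores with baseline score are typically 0.7 and 0.5, respectively"; the 0.5 is the baseline-to-follow-up correlation for pain scores.

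These two values, read this way, reproduce the plan's sample size:
- Inflation: [1 + ((1 + 0.65²) × 50 − 1) × 0.01] / 0.75 = 1.701 / 0.75 = 2.27 (stated 2.3).
- Deflation: (1 + 5 × 0.7)/6 − 0.5² = 0.50 (stated 0.5).
- 526 × 0.50 × 2.268 = 597 per arm (stated 600).

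The sample size does not depend on the present point.

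**Assumptions**
- Usual-care prevalence p0 from 10% to 80%.
- Conditional odds ratio (OR) 1.5 or 2.0.
- Covariate part of the linear predictor normal with SD s on the logit scale.

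**Covariate strength s**
- Weak covariates: s = 0.5, a latent-scale correlation of about 0.27.
- Correlation of 0.5 borrowed as a latent-scale proxy: r² = s²/(s² + π²/3), so s = √(3.290 × 0.25/0.75) = 1.05.
- Practice effect alone at ICC 0.01: s = √(3.290 × 0.01/0.99) = 0.18.

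**Formulas**
- Converted difference: OR × o/(1 + OR × o) − p0, where o = p0/(1 − p0).
- Population difference: E[expit(a + log OR + sZ)] − p0, with Z standard normal and a solved so that E[expit(a + sZ)] = p0 (Gauss-Hermite quadrature).

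Hand check of the conversion at p0 = 50%, OR 1.5: 1.5/2.5 − 0.5 = 10.0 points.

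**Results** (percentage points; relative overstatement in brackets, from unrounded values)

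| p0 | OR | Converted | Population, s = 0.5 | Population, s = 1.05 |
|---|---|---|---|---|
| 10% | 1.5 | 4.29 | 4.15 (3.2%) | 3.75 (14.4%) |
| 30% | 1.5 | 9.13 | 8.64 (5.7%) | 7.46 (22.4%) |
| 50% | 1.5 | 10.00 | 9.46 (5.7%) | 8.19 (22.1%) |
| 80% | 1.5 | 5.71 | 5.54 (3.1%) | 5.03 (13.6%) |
| 10% | 2.0 | 8.18 | 7.88 (3.8%) | 7.00 (16.8%) |
| 30% | 2.0 | 16.15 | 15.25 (5.9%) | 13.12 (23.1%) |
| 50% | 2.0 | 16.67 | 15.83 (5.3%) | 13.80 (20.8%) |
| 80% | 2.0 | 8.89 | 8.67 (2.5%) | 7.98 (11.4%) |

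- Weak covariates: about 3% to 6%, at most 0.9 points.
- Covariates as strong as r = 0.5: about 11% to 23%, at most 3.0 points.
- Practice effect alone: 0.3% to 0.8%. Added to r = 0.5, it moves the largest cell from 23.1% to 23.7%.
- Intermediate strengths at p0 = 50%, OR 1.5: s = 0.7, 1.0 and 1.3 give population differences of 9.0, 8.3 and 7.6 points against 10.0 converted, an excess of 11%, 20% and 32%. The last of these corresponds to a latent correlation of about 0.58, above the 0.5 that the protocol quotes.

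**The case against.** Five counter-arguments deserve an answer.

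1. **The prevalence may not be crude.** The protocol does not use that word, and a detailed analysis plan, not shown here, may define the conversion. This stands as a limit on the wording. The observed proportion is the natural reading because no adjusted or standardised prevalence is mentioned, but it remains a reading. The rule itself is stated in the protocol and so is open to review.

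2. **The intervals.** A reader might infer that the confidence limits of the odds ratio will be converted the same way and so ignore uncertainty in the control prevalence. The documents do not support this: nothing says how, or whether, limits for the risk difference will be formed.

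3. **The estimand.** A conditional odds ratio applied to a reference risk is a legitimate risk difference for a patient at that risk. This does not rescue the rule. The usual-care prevalence is a group average, and the result will be read as the absolute difference between the arms.

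4. **The bias is not uniform.** A reader might infer that every converted difference will be clearly exaggerated. The bias is in expectation, is small with weak predictors, and chance covariate imbalance can move a single estimate either way. Receipt of written material, for example, is collected only in the initial questionnaire and so has no earlier baseline score; a small bias is plausible there.

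5. **Narrow reach.** Most secondary outcomes are numerical scores, and counts and percentages per category will also be reported. This stands and keeps the point minor.

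**Conclusion.** The point holds as a minor one. Followed as written, the conversion can overstate the population risk difference in expectation, by an amount set by covariate strength. Almost all of the bias comes from prognostic covariates, not from clustering by practice. The direction follows from non-collapsibility and appeared in every case computed. The size rests on assumed prevalences, odds ratios and logit-scale SDs, and on borrowing a correlation quoted for pain scores as a proxy for how well covariates predict a categorical outcome. It also rests on reading the usual-care prevalence as the observed proportion.

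**What to change.** Replace the prevalence-based conversion with marginal standardisation from the mixed logistic model already fitted. Predict each participant's risk under usual care and under stratified care, average each set over the covariates and the random-effect distribution, and report the difference. Take the confidence interval from the delta method or from a bootstrap that resamples practices. Keep the odds ratios and their P values as planned.

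The cost is one sentence in the analysis plan and a small amount of post-estimation work. No new data or model is needed. If the analysis plan already defines the conversion this way, aligning the protocol sentence with it is enough.
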